#### **Concomitant medication**

Safety will be assessed based on the analysis of Concomitant medication coded according to the latest available version of the WHO-Drug dictionary.

# Statistical and Analytical Methods

## General considerations

The statistical analyses will be performed in accordance with the ICH E9 guideline and will be based on the pooled data from the individual study sites, unless otherwise stated.

The statistical analyses will be performed by an external Contract Research Organization (CRO), Venn Life Sciences, under the responsibility of the Sponsor. The full and detailed list of tables, listings and figures that will be produced is given in section 10.

### Presentation of results

The following statistics will be presented:

- For quantitative variables: number of available data, number of missing values, mean, standard deviation, median, Q1, Q3, minimum and maximum values. When relevant, confidence intervals will be calculated for the mean (Student CI) or the median (Hahn &  [Meeker](https://scholar.google.fr/citations?user=vB55GXIAAAAJ&hl=fr&oi=sra) 1991).
- For qualitative variables: number of available data, number of missing values, number and percentage of observations in each category of the variable. Except if otherwise specified, percentages will be calculated using the number of available data as denominator (i.e., not including missing values). When relevant, confidence intervals of proportions will be calculated using the Clopper-Pearson method (Clopper & Pearson 1934).

### Significance testing and estimation

The analyses of the primary efficacy criterion (overall survival) including the sensitivity analysis and of twelve months survival (secondary endpoint) will use a one-sided 0.05 type-one error rate. All other inferential tests on secondary or exploratory efficacy endpoints (see Sections 5.2.4.3 and 5.2.4.5) are presented only with an illustrative purpose and will use a two-sided 0.05 type-one error rate.

For some variables identified in this SAP, confidence intervals will be calculated with a two-sided coverage of 95%.

## Planned analysis

### Demographics and baseline characteristics

The following demographic variables will be summarised by treatment group on the FAS, SAF and the PP analysis data sets:

- Demographic data: Age and Gender and urine pregnancy test only for all women (Statistical Table 1, Listing 16.2.4.1)
- Disease characteristics (Results at screening visit for: Blood sample for HLA typing / Tumor sample for TERT and Chest/Abdomen MRI or CT / Bone scanning): HLA sample result, Biopsy sample result, scan type, scan result according to RECIST criteria (see Appendix 6: section 10.6), Bone scan, Bone scan result (Statistical Table 7, Listing 16.2.4.2):
- Medical history other than cancer under study by SOC and PT (Statistical table 10, Listing 16.2.4.5)
- Cancer history (Statistical Table 8, Listing 16.2.4.3)
- Treatment history (Statistical Table 9, Listing 16.2.4.4)

The following baseline characteristics will be described by treatment group on the FAS analysis data set:

- Laboratory test: Hematology at baseline (Statistical Table 11) and clinical chemistry at baseline (Statistical Table 12)
- Vital signs at baseline (Statistical Table 13)
- Physical examination at baseline (Statistical Table 14)
- 12–lead ECG at baseline (Statistical Table 15)
- ECOG performance status (Statistical Table 16)

### Patient disposition and study discontinuations

Patient disposition will be described using a listing (Listing 16.2.1.1), a statistical table (Statistical Table 2) and a flow chart (Figure 1).

The following variables will be tabulated for the screened population:

- Number of patients screened
- Number of patients included in the study
- Number of randomised patients, total and per treatment group
- Number of randomised patients assessed at each visit, total and per treatment group
- Number of randomised patients withdrawn from the study per reason for withdrawal, total and per treatment group

The numbers of patient within each dataset (FAS, PP and SAF), globally and by treatment group, will be provided (Statistical Table 3) together with numbers of patients assessed at each visit, globally and by treatment group. Reasons for exclusions from the FAS and PP populations will also be provided in Listing 16.2.3.1, according to ICHE3.

All protocol deviations will be tabulated by category (major or minor deviations, see Section 3.1) by treatment group for the randomized population (Statistical Table 5 and 6 respectively). All major and minor protocol deviations will also be provided in Listing 16.2.2.

### Extent of exposure and compliance

Compliance with study treatment will be computed for each subject of the FAS and the PP populations as the proportion of vaccinations actually performed (see section 8). Treatment compliance will then be analysed globally and by treatment group, as a numerical variable as well as a categorical variable (see section 8, Statistical Table 18).

To analyse the extent of exposure the following variables will be summarised by treatment group for the SAF population (Statistical Table 31):

- number of vaccinations performed
- duration (number of days) between first IP administration and last IP administration.

The number of patients administered investigational product will be summarized according to the duration of treatment, separately for each treatment groups and in total. The compliance and the duration of treatment will also listed in Listing 16.2.5.1 and Listing 16.2.5.2, respectively

### Efficacy analyses

#### Primary efficacy analysis

Initially, the primary endpoint of the study was overall survival at month 12. It was changed to overall survival following amendment Protocol dated 07 July 2015. Overall survival is defined as the time from the date of randomization to the date of death. For patients who will be alive at the time of analysis, overall survival will be censored at the time of the last available information data.

If no information is available on patient survival then every effort should be made by the investigator to obtain information on the patient vital status and the date of his/her death if relevant. In the rare cases where the information is missing, the patient will be censored at the time of the last information available.

The primary analysis (on the FAS set) will compare Overall survival using Kaplan Meier survival curves and Logrank test (Statistical Table 19, Figure 2). The primary analysis will be one-sided at the 0.05 significance level. Patients in the FAS will be analysed according to the treatment administered at the first injection and their correct strata, provided that, in the case where the actual treatment/strata differ from the randomised treatment/strata, it can be clearly justified that this difference was not influenced by knowledge of the assigned treatment.

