## Primary efficacy dataset: Full Analysis Set (FAS)

Full analysis set (FAS) (primary analysis set) – all patients who are randomised to investigational product, excluding:

- all patients who do not receive at least one dose of investigational product;
- all patients who violate a major entry criterion; the major entry criteria are defined as follow:
  - Correct diagnosis defined by inclusion criteria 2: “Documented stage IV NSCLC as defined by IASLC Lung Cancer Staging Project (7th edition) or recurrent stage I-III disease at least 6 months after resection or after the end of adjuvant chemotherapy or after standard locoregional treatment as defined by the American College of Chest Physicians”
  - Disease control after the completion of platinum-based first-line chemotherapy defined by inclusion criteria 3: “Patients treated with 4 cycles platinum based 1st line chemotherapy as defined by the American College of Chest Physicians (i.e. radiotherapy are not allowed except palliative radiotherapy of bone metastasis)” and inclusion criteria 6: “CR, PR, or SD according to RECIST criteria after the completion of platinum-based first-line chemotherapy”
  - Correct laboratory conditions for eligibility of the trial therapy defined by inclusion criteria 4: “Documented HLA-A*0201 positivity, as determined by a local laboratory” and inclusion criteria 5: “TERT-positive NSCLC, as assessed by a central laboratory; for this, availability of adequate tissue biopsy from the primary tumor, lymph nodes or distant metastases is a prerequisite”

Patients in one or more of these 3 categories will only be excluded from the FAS if it can be clearly justified that their exclusion does not introduce bias. Patients in the FAS will be analysed according to the treatment administered at the first injection and their correct strata, provided that, in the case where the actual treatment/strata differ from the randomised treatment/strata, it can be clearly justified that this difference was not influenced by knowledge of the assigned treatment.

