## Safety (SAF) dataset

The safety dataset will include all patients who received at least one injection of investigational product.

In the event of subjects having received treatments that differed from those assigned according to the randomisation schedule, then the safety analyses should be conducted according to the treatment actually received (As Treated analysis) rather than according to the randomisation groups.

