#### Sensitivity efficacy analysis

To assess the robustness of the main analysis, several sensitivity analyses will be performed:

- The same primary analysis will be performed on the Per-Protocol set (Statistical Table 20, Figure 3).
- In case of randomisation errors (patients not receiving the treatment attributed by randomisation) and/or stratification errors (patients not attributed to the correct strata at the time of randomisation), the primary analysis will be repeated, according to treatment attributed by randomisation and strata used for the randomisation). If no patient show randomisation or stratification errors, this sensitivity analysis will not be applicable.
- Cox-model regressions of overall survival adjusted for the stratification factors and prognostic factors on the FAS and PP sets, a two-sided 90% confidence interval of the hazard ratio of the treatment effect will be provided (Statistical Table 21, Figure 4)
  - Stratification factors:
    - Response to first line chemotherapy: objective response vs. stable disease,
    - Squamous vs. non-squamous,
    - Stage IV vs. recurrent stage I-III
  - Prognostic factors:
    - Level of tumor TERT expression: low vs. high,
    - Vaccine specific immune response status: naturally occurring response vs. absence of naturally occurring response

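### The single definitive efficacy test groups patients by treatment received at the first injection; the randomised comparison is only a conditional sensitivity analysis

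*SAP*

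**What the plan says.** Section 5.2.4.1 defines the primary analysis: "The primary analysis (on the FAS set) will compare Overall survival using Kaplan Meier survival curves and Logrank test". It then sets the grouping rule: "Patients in the FAS will be analysed according to the treatment administered at the first injection and their correct strata". Where the actual treatment differs from the randomised one, the rule applies on condition that "it can be clearly justified that this difference was not influenced by knowledge of the assigned treatment". The FAS definition in section 3.2 carries the same rule and the same condition.

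The comparison by randomised arm is in section 5.2.4.2. If randomisation or stratification errors occur, "the primary analysis will be repeated, according to treatment attributed by randomisation and strata used for the randomisation". Otherwise: "If no patient show randomisation or stratification errors, this sensitivity analysis will not be applicable".

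Three other places bear on this:

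- Section 5.3.5 states that the primary efficacy analysis is the only one used for definitive efficacy conclusions.
- Section 3.4 already specifies as-treated grouping for the safety set.
- Section 5.3.2 imputes missing 12-month survival according to the arm to which the patient was randomised.

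**The concern.** In a superiority test, the groups are comparable because randomisation formed them. Treatment received is settled later, at the first injection, while section 5.2.4.1 times overall survival from randomisation. Moving a mis-dosed patient to the other arm lets a post-randomisation event define the groups. If the two groupings gave different answers, the SAP would let the as-treated one decide.

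The proviso narrows the rule but does not make the randomised arm the default. It covers one cause of error, knowledge of the assignment, and leaves other causes aside. It also leaves a gap: for a patient whose mismatch cannot be so justified, the SAP does not say whether the patient reverts to the randomised arm, is excluded, or is handled otherwise. Arm membership in the one decisive test should not depend on an open judgement.

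**Working it through.** The point concerns the analysis principle and rests on no stated number. The arithmetic below only sizes it.

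**1. Where the rule leads.**

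| Situation | Primary (5.2.4.1) | Sensitivity (5.2.4.2) |
| --- | --- | --- |
| No wrong-treatment errors | Received and randomised treatment coincide | Same grouping by treatment |
| Error, proviso met | Arm received | Randomised arm |
| Error, proviso not met | Not stated | Randomised arm |

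Only the second and third rows matter. In both, the SAP ranks the randomised comparison below the decisive one.

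There is a knock-on inconsistency for 12-month survival. A mis-dosed FAS patient with missing status would be imputed under the randomised arm (section 5.3.2) but counted under the arm received (section 3.2).

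**2. The SAP's stated power.** Inputs from the revised sample-size calculation: 12-month survival 43% and 58%, exponential; 100 evaluable patients per arm; 39 months' accrual (taken as uniform); 6 months' minimum follow-up; one-sided alpha 0.05.

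- Hazards: −ln(0.43)/12 = 0.0703 and −ln(0.58)/12 = 0.0454 per month, so HR = 0.645.
- Probability of death by the analysis, per arm: 1 − (e^(−6λ) − e^(−45λ))/(39λ) = 0.776 and 0.643.
- Expected deaths: 100 × (0.776 + 0.643) ≈ 142.
- Schoenfeld power: Φ(√142/2 × |ln 0.645| − 1.645) = Φ(0.96) ≈ 83.2%. The Freedman version gives 82.2%.

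The SAP states approximately 82.5%, so its figure reproduces.

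**3. How many patients could move.** The SAP gives no error rate. As an assumption, one to four wrong-treatment errors among 220 patients is 1/220 = 0.5% to 4/220 = 1.8%.

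**4. What the as-randomised analysis costs in power.** Assume a share m of each arm receives the other treatment and takes on its survival. The 12-month survival by randomised arm is then (1−m)×0.43 + m×0.58 and (1−m)×0.58 + m×0.43. Deaths are held at 142.

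| m (assumed) | Survival by arm | HR | Power |
| --- | --- | --- | --- |
| 0 | 0.4300, 0.5800 | 0.645 | 83.2% |
| 1% | 0.4315, 0.5785 | 0.651 | 81.9% |
| 2% | 0.4330, 0.5770 | 0.657 | 80.4% |
| 5% | 0.4375, 0.5725 | 0.675 | 75.8% |

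The loss is 1.4, 2.8 and 7.4 points before rounding. Rates of 1% to 2% are closest to the range in step 3.

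**5. What as-treated grouping could do to the type I error.** This was simulated under no treatment effect with 220 patients, the same accrual and follow-up, two or four mis-dosed patients, and 20,000 runs per case.

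- Errors at random: rejection rate 4.8% to 5.1% against a nominal 5%.
- Errors confined to poor-prognosis patients, in either direction: 5.0% to 5.2%.
- Every error a Vx-001 patient given placebo, and all on the worst-prognosis patients: 6.6% with two errors and 8.8% with four. These two figures depend on how worst prognosis is defined; a stricter definition gives higher ones.

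**The case against.** The strongest defence is that the rule can hardly do harm here. Allocation is by IWRS, and investigators, patients, the sponsor, monitors, data management and biostatistics are all blind. The proviso excludes errors driven by knowledge of the assignment. The simulations show no inflation unless errors are both one-directional and concentrated in the sickest patients, a pattern the SAP gives no reason to expect. If any error occurs, the as-randomised repeat is mandatory, so the reader would see both results. All of this stands, and it limits the practical weight of the point. It does not explain why the comparison with the weaker protection should be the decisive one.

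Three stronger readings are tempting but not supported:

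- A reader might infer that applying the rule requires breaking the blind. It does not. Whether knowledge of the assignment influenced an error can be judged from the fact and circumstances of the mismatch. The arm received is needed only when the analysis is run, after the first database lock, when unblinding is planned.
- A reader might object equally to the use of corrected strata. Section 5.2.4.1 names a logrank test without calling it stratified, so the choice of strata does not change the primary test as written. Correcting a stratum also moves nobody between arms.
- A reader might infer that the type I error is materially inflated. The SAP gives no error rate, and only the extreme pattern in the simulation produces inflation.

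**Conclusion.** The point holds for treatment grouping. Sections 3.2 and 5.2.4.1 group the primary analysis by treatment received at the first injection, under a proviso with no stated outcome when it fails. Section 5.2.4.2 leaves the randomised comparison as a conditional check, and no other section restores it.

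The effect is zero if no patient receives the wrong treatment. With a handful of errors under double blinding it is probably small and would matter only for a result near the significance threshold. That judgement assumes few errors with no systematic link to prognosis; the SAP gives no figure for either. The case for change is that the decisive test should rest on randomisation and leave no discretion over arm membership.

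The change should not be read as producing full intention-to-treat. The FAS can still leave out "all patients who do not receive at least one dose of investigational product" and patients who violate a major entry criterion, where exclusion is justified as unbiased.

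**What to change.** - Sections 3.2 and 5.2.4.1: analyse FAS patients by randomised arm, with no proviso.
- Section 5.2.4.2: make grouping by treatment received at the first injection the sensitivity analysis, run if any wrong-treatment error occurs.
- Section 3.4: leave as-treated grouping for safety unchanged.
- Appendices 1 and 2: add a table and figure for the sensitivity analysis. The present as-randomised repeat has no entry of its own; section 5.2.4.2 ties Table 20 and Figure 3 to the per-protocol analysis.

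Both analyses are already planned, so no new data are needed and sample size and alpha do not change. The cost is a short text edit plus, if errors occur, the modest power loss shown above. The edit should be made before database lock and unblinding. It also brings the 12-month survival analysis into line with the imputation by randomised arm in section 5.3.2.

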#### Sensitivity efficacy analysis

To assess the robustness of the main analysis, several sensitivity analyses will be performed:

- The same primary analysis will be performed on the Per-Protocol set (Statistical Table 20, Figure 3).
- In case of randomisation errors (patients not receiving the treatment attributed by randomisation) and/or stratification errors (patients not attributed to the correct strata at the time of randomisation), the primary analysis will be repeated, according to treatment attributed by randomisation and strata used for the randomisation). If no patient show randomisation or stratification errors, this sensitivity analysis will not be applicable.
- Cox-model regressions of overall survival adjusted for the stratification factors and prognostic factors on the FAS and PP sets, a two-sided 90% confidence interval of the hazard ratio of the treatment effect will be provided (Statistical Table 21, Figure 4)
  - Stratification factors:
    - Response to first line chemotherapy: objective response vs. stable disease,
    - Squamous vs. non-squamous,
    - Stage IV vs. recurrent stage I-III
  - Prognostic factors:
    - Level of tumor TERT expression: low vs. high,
    - Vaccine specific immune response status: naturally occurring response vs. absence of naturally occurring response

#### Secondary efficacy analyses

The following secondary endpoints will be analysed on the FAS and PP sets:

- Twelve months survival:

A patient overall survival (success) at 12 months is defined as a patient who is alive as confirmed by the visit at week 52. If the patient misses the visit or has been lost to follow-up, every effort will be made by the investigator to ascertain whether the patient was alive on the theoretical date of his/her week 52 visit.

A one-sided Pearson’s chi-squared test of proportions will be used to compare the survival rate of the Vx-001 treated group to the placebo treated group at 12 months (Statistical Table 22).

- Time to Treatment Failure (TTF)

Time to treatment failure is defined as the interval between the date of first study treatment and the date of early withdrawal, or the date of the initiation of other anti-tumor treatment, whichever will come first. Patients without early withdrawal or initiation of another anti-tumor treatment will be censored at their last tumor assessment of target or non-target lesions. If patient have neither any failure events nor any post-baseline tumor assessment censoring time will be set to zero.

All these secondary endpoints are "time to event" endpoints and will be analyzed via

- Kaplan-Meier curves by treatment arm and log-rank test for their comparison (Statistical Table 23, Figure 5)
- Cox regression model where the treatment effect will be included and also the stratification factors and prognostic factors specified in the section 5.2.4.2 will be also included. Via this Cox model a two-sided 95% confidence interval of the hazard ratio of the treatment effect will be provided for both population (FAS and PP sets) (Statistical Table 24, Figure 6).

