### **Major protocol deviations**

Major protocol deviations are defined as deviations liable to prevent or change the interpretation of the results of the primary efficacy analysis of the study. The following deviations may be considered as major (this list is not exhaustive and will be reviewed at the time of the blind review meeting):

- non compliance with the inclusion or non inclusion criteria
- non compliance with the randomisation procedure
- non compliance with study treatment
- no post-baseline data for the primary efficacy endpoint
- intake of forbidden medication

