## Per-protocol (PP) dataset

Per-protocol (PP) analysis – all patients in the FAS who satisfy the following criteria:

- no major protocol deviations;
- good treatment compliance (early treatment discontinuations will only be considered for exclusion from the PP dataset if the reasons for early treatment discontinuation are unrelated to the assigned treatment).

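### The per-protocol analysis of time to treatment failure can exclude patients on post-randomisation criteria that overlap the endpoint event

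*SAP*

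**What the plan says.** SAP 5.2.4.3 (Secondary efficacy analyses) introduces twelve-month survival and TTF with: "The following secondary endpoints will be analysed on the FAS and PP sets". TTF runs from first study treatment to "the date of early withdrawal, or the date of the initiation of other anti-tumor treatment, whichever will come first". It is analysed by Kaplan-Meier, log-rank and an adjusted Cox model (Tables 23-24, Figures 5-6), with the Cox interval requested for both sets.

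SAP 3.3 (Per-protocol dataset) starts from the FAS and requires "no major protocol deviations" and good treatment compliance. It adds that early discontinuations "will only be considered for exclusion from the PP dataset if the reasons for early treatment discontinuation are unrelated to the assigned treatment".

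SAP 3.1.1 (Major protocol deviations) gives a non-exhaustive list, introduced by "The following deviations may be considered as major". The list includes non-compliance with study treatment and "intake of forbidden medication". SAP 3.1.3 (Study treatment discontinuations) names a major protocol violation and withdrawal of consent among the reasons for stopping treatment.

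**The concern.** For overall survival, stopping treatment is not the event, so a PP set that drops some early discontinuers at least does not delete deaths by definition. For TTF, stopping early is the event. A patient who leaves the PP set because of early discontinuation takes a failure out of the analysis, together with the failure-free time before it. The PP analysis then selects on the outcome that it measures.

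Two things are at stake. PP TTF looks longer than it was. If removals are unequal between arms and concentrated early, the PP hazard ratio also moves away from the FAS hazard ratio because of the exclusion rule. A difference between the two sets on TTF would then be hard to interpret.

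**Working it through.** **1. Event definition against exclusion rules**

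| Reason for leaving treatment, or conduct | TTF event (5.2.4.3)? | Can lead to PP exclusion? |
|---|---|---|
| Consent withdrawn, judged unrelated to treatment | Yes | Yes, may be considered (3.3) |
| Stopped for a major protocol violation | Yes | Yes, if classed as a major deviation (3.1.1, 3.3) |
| Other anti-tumour drug started while on vaccine | Yes | Only if it counts as forbidden medication and is classed as major |
| Missed vaccinations after stopping early | The stop is the event | Possibly: the level that counts as good compliance is left to the data review (Section 3), and Section 8 gives no derivation |
| Discontinuation judged related to treatment | Yes | Not on the discontinuation ground (3.3) |
| Progression | Yes, through withdrawal | Not listed as a deviation |

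The overlap is real but covers only some TTF events. The limit to unrelated reasons does not remove it, because TTF counts early withdrawal for any reason.

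**2. The plan's figure**

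The SAP states no figure for TTF. The relevant one is the 10% loss from FAS to PP in the revised sample-size calculation: 220 × 0.10 = 22 excluded and 198 left, which agrees with the stated approximate 200.

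**3. Effect on the median**

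Assume exponential TTF with median m, and that a fraction f of patients is removed, all of them failing before the new median. The PP median t then solves S(t) = 0.5 × (1 − f), so t = m × [1 + log2(1/(1 − f))].

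- f = 0.10 (all 22): log2(1/0.90) = 0.152, so m = 4.0 becomes 4.61 months and m = 6.0 becomes 6.91 months, about +15%.
- f = 0.05 (half of them): log2(1/0.95) = 0.074, about +7%.

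Simulation with 11 removed per arm, all failing before 3.45 months (15 weeks), gave 4.62 and 6.92-6.93 months. The medians of 4 and 6 months are assumptions; the relative change does not depend on them.

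**4. Hazard ratio and error rate with no true difference** (110 per arm, medians 4 or 6 months, early failures removed)

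- 22 removed regardless of arm (6,000 trials per scenario): mean HR 1.00, two-sided rejection 5.5-5.7%. With 11 removed: 5.1-5.3%.
- Split imposed, Vx-001/placebo (3,000 trials per scenario): 8/14 gives HR 1.05-1.06. 17/5 gives 0.89-0.91 and 5/17 gives 1.10-1.12, with rejection of 11.5-13.0% for these two.
- Probability of 17/5 or worse in either direction if the 22 fall by chance, Binomial(22, 0.5): 2 × (1 + 22 + 231 + 1,540 + 7,315 + 26,334)/2^22 = 70,886/4,194,304 = 1.7%.

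**5. A real difference in early withdrawal** (assumptions: 110 per arm, other failures with median 4 months in both arms, discontinuation within 2 months, every discontinuer removed from PP, 3,000 trials)

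| Discontinue early, placebo vs Vx-001 | FAS HR | PP HR |
|---|---|---|
| 10% vs 10% | 1.00 | 1.00 |
| 5% vs 15% | 1.10 | 1.02 |
| 5% vs 25% | 1.22 | 1.04 |
| 15% vs 5% | 0.91 | 0.98 |

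If discontinuation instead has a constant hazard over time, FAS and PP hazard ratios differ by about 0.01 or less. The hazard ratio is distorted when removals are both unbalanced and clustered early.

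**The case against.** The exclusions are conditional. Discontinuation is only considered, and only for unrelated reasons; the listed deviations only may be major; classification takes place before unblinding. Progression and treatment-related discontinuation are not grounds for exclusion, and the SAP does not say that anti-tumour treatment started after stopping vaccine is forbidden medication. The 10% loss covers every reason, including eligibility and randomisation errors. The FAS analysis of TTF is already planned. SAP 5.3.5 makes all tests other than the primary illustrative, and SAP 5.3.6 gives the PP set a robustness role for the primary analysis only.

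All of this stands, and it limits the point. It does not remove it. Blind review prevents classification by known arm but not selection on the outcome, and nothing in the SAP keeps TTF failures in the PP set.

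A reader might infer that PP removes every patient who fails. The text does not support that: exclusion is possible, not automatic, and concerns a subset of events. A reader might also infer from the imposed 17/5 split that the test's error rate is 12-13%. That figure is conditional on an imbalance with probability of about 1.7% under arm-neutral exclusion, where the error stays near 5-6%.

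**Conclusion.** The point holds as a should-fix matter of limited impact. As planned, the PP analysis of TTF can drop patients on criteria that overlap the event, and every patient dropped for early discontinuation is a deleted failure. The pooled median is lengthened by about 15% if all 22 expected exclusions are early failures under exponential TTF, and by less if fewer are. Under no effect and arm-neutral exclusion the hazard ratio stays near 1.00 and the error near 5-6%. If early exclusions differ by arm, the hazard ratio is distorted: in the illustrations, an FAS value of 1.22 caused by withdrawal alone shrinks to 1.04 in PP. These sizes rest on assumed medians, timing and arm differences, since the SAP gives none for TTF. The primary analysis is unaffected.

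**What to change.** In SAP 5.2.4.3, analyse TTF on the FAS only, and limit Tables 23-24 and Figures 5-6 accordingly.

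If a PP view is kept, define a PP set for TTF using only deviations fixed at or before randomisation (eligibility, randomisation procedure). Patients with later discontinuation, non-compliance or other anti-tumour treatment stay in that set, and early withdrawal and new anti-tumour treatment count as events. The PP set for overall survival stays as it is.

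The cost is one sentence and the loss or redefinition of one supportive analysis of a secondary endpoint.
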